### Monitoring

To monitor our study, a Steering Committee (SC) and a Data Monitoring (DMC) will be appointed. The SC will comprise all researchers involved in this publication and will be led by MH, an experienced researcher with expertise in clinical research. On regular meetings the SC will monitor the study procedures and ensure that the trial is being conducted according to the study protocol. On this behalf, areas of interest are the recruitment processes of all different participants (patients, MHS, GP), intervention delivery, data collection, and communication aspects with both the collaboration partners and the trial participants. The primary aim of the SC is to facilitate the smooth running of the trial.

The DMC will comprise four members including one researcher from the Institute of Medical Biometry and Informatics in Heidelberg. They will have clinical, research, and statistical expertise. They will regularly monitor quality and plausibility of the collected data by sighting data exports from the electronic data collection platform. Since the intervention used in our trial study is evidence-based, successfully piloted, and all patients will be linked in with their GP, no interim analyses or auditing are planned. Close communication with the MHS additionally to the biweekly supervision will assess adverse events. We will record all adverse events with respect to relation to study, severity, potential for the event to have been anticipated, and action taken. Serious adverse events will be reported to the Ethics Committee.

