**Methods:**

In an individually randomised, prospective, two-arm superiority trial with parallel group design, *N* = 320 patients with anxiety and/or depressive disorder will be recruited in general practices in Germany. The intervention includes a newly developed treatment model based on video consultations with focus on diagnostics, treatment planning, and short-term intervention by mental health specialists. We will systematically compare the effectiveness, cost-effectiveness, and adverse effects of this new model with usual care by the GP: the primary outcome is the absolute change in the mean depressive and anxiety symptom severity measured on the Patient Health Questionnaire Anxiety and Depression Scale (PHQ-ADS) from baseline to 6 months after baseline assessment. Follow-up in both groups will be conducted by blinded outcome assessors at 6 months and 12 months after baseline. The main analysis will be based on the intention-to-treat principle. We will optimise the likelihood of treatment effectiveness by strict inclusion criteria for patients, enhanced intervention integrity, and conducting a process evaluation.

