#### Secondary outcomes

Secondary outcomes include differences of the absolute change in mean depressive and anxiety symptom severity on the PHQ-ADS at 12 months between both study arms. At 6 and 12 months after baseline assessment, we will also calculate the absolute change in mean depressive and anxiety symptom severity on the PHQ-9 and GAD-7, respectively along with differences in mean burden of specific somatic complaints (Somatic Symptom Disorder–B Criteria Scale, SSD-12 [66]), recovery (Recovery Assessment Scale, RAS-G [43]), health-related quality of life (SF-12 questionnaire [67], and EQ-5D 5 L [68]), quality and patient-centredness of chronic illness care (Patient Assessment of Chronic Illness Care–Short Form, PACIC–Short Form [69]), adverse effects (Inventory for the Assessment of Negative Effects of Psychotherapy, INEP [70]), and health service use (Questionnaire for the Assessment of Medical and non-Medical Resource Utilisation in Mental Disorders, FIMPsy [71]) between both study arms. The cost-effectiveness of the primary care embedded MHSVC model of care compared to usual care over the study period will comprise additional secondary outcomes.

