The quality and patient-centredness of chronic illness care will be measured using the PACIC–Short Form which consists of 11 items with each item scored on a 5-point Likert scale (from 1 = “no/never” to 5 = “yes/always”) [69]. Overall mean scores are in the range of 1 to 5 with higher scores indicating better outcomes. The PACIC-Short Form has high internal consistency (Cronbach’s *α* = 0.87) and convergent validity with the established 20-item PACIC.

We will measure adverse effects using the INEP [70]. The INEP comprises 21 items that are rated in a 7-step bipolar format (–3 = “definitely a negative effect” to 3 = “definitely a positive effect”) to detect not only deteriorations but also improvement or lack of change and to prevent negative priming. If a bipolar format is not appropriate to the content, a 4-stage unipolar response format is applied instead (0 = “disagree/not applicable” to “3 = fully agree”). For each item, the attribution is stated from the patient’s perspective (“What caused this outcome?” – “the therapy” or “other circumstances in life”). Only negative effects that are attributed by the patient directly to the psychotherapeutic treatment are considered for the analysis.

Health service use will be measured using the FIMPsy questionnaire which is particularly suited for patients with mental disorders [71, 76]. It assesses the following services in the preceding 6 months retrospectively: psychiatric counselling, assisted living, and occupational integration. FIMPsy also captures contacts with outpatient and inpatient medical providers as well as the intake of medication.

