A major methodological consideration for the PROVIDE-C trial was weighing an individually randomised design vs. a cluster-randomised design. Randomising individuals who are recruited from the identical general practice, where the GP is not masked to the participant’s study arm, may bear a greater risk of contamination between arms than randomising a group of individuals that do not belong to the same practice. While we did consider designing a cluster-randomised trial, we eventually opted for an individually randomised trial. Specifically, we decided to proceed in this way for several reasons: First, while the GP will recruit individuals, she or he will not be involved in delivering the intervention and will have no access to the allocation schedule. We consider this as an advantage over cluster-randomised trials which are associated with a significant risk of recruitment bias. Second, we applied a recently developed framework for identifying the risk of contamination [93]. The framework accounts for three possible sources of contamination: (a) participants in the control arm, (b) participants in the intervention arm, and (c) therapists in the intervention arm. In sum, considering all three sources, we consider the overall risk of contamination in the PROVIDE-C trial low. Third, prior work shows that in therapy trials risk of contamination occurs rarely and is generally low across trials [93]. Notwithstanding, current evidence supports the decision to choose an individually randomised controlled trial rather than a cluster-randomised trial based on the observation that the latter designs are only more efficient when contamination exceeds 30% [94, 95]. Fourth, considering the potential drawbacks of implementing cluster-randomised trials in terms of ethical issues, the need for a larger sample size, and recruitment bias, recent recommendations promote individually randomised trials when the intervention accessibility (timely video consultations with mental health specialists are not available in routine primary care in Germany and can only be accessed by permission of the study team) is limited and complex to deliver (we used highly trained mental health specialists who delivered a multi-component manual-based intervention and had no contact at all with participants from the control arm) [93, 96–98]. In PROVIDE-C, GPs will have no access to the trial intervention; therefore, the risk that GPs may implement some of the intervention to patients allocated to the control arm is small. At any rate, we will (a) measure the degree of potential contamination by capturing the number of patients in the control arm who receive video consultations from their GP and (b) consider the clustered structure of patients in practices as random effect in the regression analysis.

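### The only stated source of adverse event reports is the mental health specialists, who do not see controls, so no route is given for control-arm events or for events after the last session

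*Protocol article*

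**What the plan says.** The article has two separate streams of harms data.

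**Adverse events** are dealt with under Monitoring. The stated source is the MHS: "Close communication with the MHS additionally to the biweekly supervision will assess adverse events". Two undertakings follow, neither restricted to an arm: "We will record all adverse events with respect to relation to study, severity, potential for the event to have been anticipated, and action taken", and "Serious adverse events will be reported to the Ethics Committee". The Discussion, in arguing that contamination is unlikely, says that the MHS "had no contact at all with participants from the control arm".

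**Adverse effects** are a secondary outcome, measured with the INEP at 6 and 12 months and compared between arms (Outcomes and Measures, Secondary outcomes). This is the endpoint behind the statement in the Abstract: "We will systematically compare the effectiveness, cost-effectiveness, and adverse effects of this new model with usual care by the GP". Data collection covers both arms, and under Masking the post-measurement interviews are done by research assistants who do not know the allocation.

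The intervention is five sessions at two-week intervals, over approximately 8 weeks (Intervention arm; Intervention integrity). Follow-up runs to 12 months. The Dissemination policy commits the results paper to the CONSORT extension for adverse effects.

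**The concern.** A plan that undertakes to record all adverse events needs a source that can see all patients. The source named here sees one arm, and that arm for only part of follow-up. A hospital admission or a suicidal crisis in a control patient, or in an intervention patient at month 9, has no stated path into the adverse event record or to the Ethics Committee.

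Two things are at stake. Serious event reporting would be incomplete in a way that depends on allocation. And if the recorded events are tabulated by arm, as a reader of the results paper may well expect, the table would reflect who was being watched more than what the treatment did. The distortion would run against the intervention.

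**Working it through.** The plan gives no figure for adverse events, so there is none to reproduce. The check is mainly a comparison of passages.

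**1. Who can report an event, and when**

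| Patients and period | Contact with the stated source (MHS)? | Basis |
|---|---|---|
| Intervention, during sessions | Yes | Five sessions, 4 intervals × 2 weeks = 8 weeks (Intervention arm; Intervention integrity) |
| Intervention, last session to month 12 | None scheduled | Sessions end; the MHS sends a case summary to the GP |
| Control, baseline to month 12 | No | Discussion |

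Recruitment (Primary care patients) puts the individual intervention period at three months instead. Either figure ends well before the 6-month assessment. Supervision continues every two weeks, but it can only pass on what the MHS know about their own patients. Monitoring notes that all patients are linked with their GP, but describes no GP reporting of events.

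**2. What is measured in both arms**

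- INEP: patient-reported, 6 and 12 months.
- PHQ-ADS: symptom worsening. It contains all nine PHQ-9 items, including item 9, which the exclusion criteria use for risk of self-endangerment.
- FIMPsy: inpatient and outpatient contacts over the preceding 6 months.
- Routinely collected general practice data (Concomitant care).

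These show that much of the relevant information exists for controls. None of them is designated as a source of adverse events, and none is said to carry the assessment of relatedness, severity, anticipation and action that Monitoring requires.

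**3. Size, as an illustration only**

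Inputs: 160 patients per arm (320 at 1:1, from the article). The true event rate *r* is taken as equal in both arms, and the detection probability *d* is set for each arm; both are assumptions. Expected recorded events per arm = 160 × *r* × *d*.

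| *r* | MHS detection | Control detection | Recorded events | Spurious difference (percentage points) |
|---|---|---|---|---|
| 5% | 100% | 0% | 8 v 0 | 5 |
| 5% | 80% | 0% | 6.4 v 0 | 4 |
| 5% | 80% | 25% | 6.4 v 2 | 2.8 |
| 5% | 50% | 50% | 4 v 4 | 0 |
| 10% | 80% | 0% | 12.8 v 0 | 8 |
| 20% | 80% | 0% | 25.6 v 0 | 16 |

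With no detection in controls and MHS detection between 50% and 100%, the spurious difference runs from 2.5 points (*r* = 5%, 50% detection) to 20 points (*r* = 20%, full detection).

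If such counts were tested, the two-sided Fisher exact p-value for *x* v 0 with equal arms is 2 × C(160, *x*) / C(320, *x*):

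- 8 v 0 (5%): p = 0.007
- 6 v 0 (3.75%): p = 0.030
- 5 v 0 (3.1%): p = 0.061

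The article does not plan this test. The figures only show how few events would be needed to mislead.

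**The case against.** The strongest objection is that the comparison the article promises does not use the MHS route at all. A reader might infer from the Abstract and Monitoring together that harms are found only through the MHS and that the comparison of harms is biased by design. The documents do not support that. The comparison is of adverse effects by the INEP, collected from patients in both arms; Monitoring describes recording and reporting of adverse events and announces no between-arm test of them. This objection stands, and it limits the point to the adverse event stream.

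A reader might also infer that deterioration in controls would go unseen. That is wrong too. Controls receive unrestricted usual care, and worsening, PHQ-9 item 9 and inpatient contacts are measured in both arms at 6 and 12 months. What remains is that these data are not treated as adverse events.

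Third, the article condenses a fuller protocol that may describe GP reports or safety questions at interview, and Monitoring does not say that the MHS are the sole source. That is fair, and it is why this is a correction to a stated route and not proof that control events will be lost. But the article does more than leave the matter open: it names a route, the route reaches one arm, and the next sentence claims full coverage.

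The INEP has a possible asymmetry of its own, since "Only negative effects that are attributed by the patient directly to the psychotherapeutic treatment are considered for the analysis" and controls may have had no psychotherapy. That is a different mechanism. It neither causes nor cures the gap described here, although it means the INEP is a poor substitute for event reporting that is the same in both arms.

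**Conclusion.** The point holds in limited form. As written, the plan gives no way to learn of adverse events or serious adverse events in the control arm, or in the intervention arm after the last session, while undertaking to record them all. Counts from the stated route would not be comparable between arms, and any difference would tend to make the intervention look worse. With equal true rates of 5% to 20% and no control-arm detection, the artefact would be 2.5 to 20 percentage points. That range rests on assumed rates and detection probabilities, and it matters for inference only if someone compares the counts.

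The INEP comparison, the PHQ-ADS analysis and the service-use data are not affected. This is a cheap improvement to safety ascertainment and reporting, and it does not undermine the trial's main conclusions.

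**What to change.** 1. Add the same short set of adverse event and serious adverse event questions for both arms to the 6- and 12-month telephone interviews. Place them directly after the PHQ-ADS, so that an answer that reveals the allocation cannot influence the primary outcome. Carry them on the mailed questionnaire that the Retention section allows.
2. Name the routine general practice data, already collected in both arms, as a second source. It would also cover patients who miss an interview.
3. State that any between-arm comparison of events uses only these two sources.
4. Keep the MHS reports for prompt notification, present them separately and descriptively for the intervention arm, and state that they are not compared between arms.
5. If the full protocol already provides a control-arm route, say so in one sentence under Monitoring.

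The cost is a few extra interview items and a short amendment to the protocol and the analysis plan. No new visits or staff are needed.

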### Ethics

This trial has undergone ethical scrutiny and has been approved by the Medical Faculty of the University of Heidelberg Ethics Committee (S-923/2019). Additionally, considering that the study will take place in routine general practice, we have obtained the ethical approval of the State Chamber of Physicians Baden-Wuerttemberg. Approvals from Hesse and Rhineland-Palatinate, where recruitment will start later, are pending. Eligible patients will receive a hardcopy of a plain language statement outlining the potential risks and benefits of participating in the PROVIDE-C trial and give written informed consent to participate in the study. Confidentiality of participants will be protected by assignment of an identification number to each participant. Participants’ study information will not be released outside of the study without permission, except where maintaining confidentiality endangers the health or safety of the participant or someone else.

After the individual intervention period, all patients, who need further psychological treatment or mental health support, can approach the psychosomatic outpatient clinic at the University Hospital Heidelberg. Furthermore, one main component of the intervention is the consideration and discussion between MHS and patient about the type of a potential follow-up treatment.

### Dissemination policy

Regardless of the magnitude or direction of effect, the results of this trial will be presented at relevant national and international conferences and as published articles in peer-reviewed journals. Publication of the study results will be based on the CONSORT-SPI 2018 statement for social and psychological interventions and the CONSORT extension for adverse effects [42, 92]. The progress and the results of the trial will be disseminated to the participating general practices and MHS in a trial newsletter and via personal visits and to patients, caregivers, and wider audiences via social media. To reach health care policy and practice audiences (e.g. government bodies) concerning the scale-up of the model, we will present the findings at policy maker- and service provider-run conferences. Aiming at directly informing the work of policy makers and practitioners, we will report the findings in plain language formats to them and compile an executive summary drawing together key findings of all aspects of the intervention with a series of journal articles included as appendices.

## Discussion

Although an array of effective treatments is available, depression and anxiety disorders still cause a notable burden to many people worldwide. In contrast to traditional specialised services, mental health service models integrated into primary care succeed in engaging hard-to-reach patient groups where they enter the health care system. However, models with mental health specialists located on site are not feasible for the large number of smaller, single-handed, and/or rural or remote general practices in many countries throughout the world. Instead, primary care mental health featuring MHSVC may be more suitable for these practices and increase the accessibility to specialised mental health care for the increasing number of multimorbid patients.

We have therefore developed and piloted a service model that integrates MHSVC into primary care for treating patients presenting with depression and anxiety. In the PROVIDE-C trial, we will test whether this model is a clinically effective and cost-efficient way of reducing depressive and anxiety symptom severity, relative to usual care. The main strength of this trial is its sound foundation in both a preimplementation and a feasibility study and the resulting feedback from the key stakeholders. Although the trial is performed in routine practice settings, we will optimise the likelihood of treatment effectiveness by strict inclusion criteria for patients and enhanced intervention integrity.

A major methodological consideration for the PROVIDE-C trial was weighing an individually randomised design vs. a cluster-randomised design. Randomising individuals who are recruited from the identical general practice, where the GP is not masked to the participant’s study arm, may bear a greater risk of contamination between arms than randomising a group of individuals that do not belong to the same practice. While we did consider designing a cluster-randomised trial, we eventually opted for an individually randomised trial. Specifically, we decided to proceed in this way for several reasons: First, while the GP will recruit individuals, she or he will not be involved in delivering the intervention and will have no access to the allocation schedule. We consider this as an advantage over cluster-randomised trials which are associated with a significant risk of recruitment bias. Second, we applied a recently developed framework for identifying the risk of contamination [93]. The framework accounts for three possible sources of contamination: (a) participants in the control arm, (b) participants in the intervention arm, and (c) therapists in the intervention arm. In sum, considering all three sources, we consider the overall risk of contamination in the PROVIDE-C trial low. Third, prior work shows that in therapy trials risk of contamination occurs rarely and is generally low across trials [93]. Notwithstanding, current evidence supports the decision to choose an individually randomised controlled trial rather than a cluster-randomised trial based on the observation that the latter designs are only more efficient when contamination exceeds 30% [94, 95]. Fourth, considering the potential drawbacks of implementing cluster-randomised trials in terms of ethical issues, the need for a larger sample size, and recruitment bias, recent recommendations promote individually randomised trials when the intervention accessibility (timely video consultations with mental health specialists are not available in routine primary care in Germany and can only be accessed by permission of the study team) is limited and complex to deliver (we used highly trained mental health specialists who delivered a multi-component manual-based intervention and had no contact at all with participants from the control arm) [93, 96–98]. In PROVIDE-C, GPs will have no access to the trial intervention; therefore, the risk that GPs may implement some of the intervention to patients allocated to the control arm is small. At any rate, we will (a) measure the degree of potential contamination by capturing the number of patients in the control arm who receive video consultations from their GP and (b) consider the clustered structure of patients in practices as random effect in the regression analysis.

Further challenges of this trial may include the recruitment and retention of patients [99]. If the PROVIDE model proves to be clinically effective and cost-effective, broad implementation into routine primary care could contribute to mitigating the geographical and temporal barriers for optimised diagnostics and treatment for two of the most pressing health conditions globally.

